### Planned size

The sample size required for this study was calculated to be 600 cases; based on a previous study showing that 52% of females aged 17–18 years had VDD (serum 25(OH)D level below 20 ng/mL) [8], and assuming that the proportion of VDDs is also 50% in the study population, we expect 300 individuals to have VDDs. Finally, we expect 30% of the subjects to drop out of the study due to incomplete data sets and withdrawal of consent.

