### Statistical analysis

The continuous variable will be expressed as mean ± standard deviation or median (interquartile range), and a categorical variable as frequency (percentage). Mann-Whitney U test and Kruskal-Wallis test will be used for the comparison between two groups and more than two groups, respectively. The chi-squared test will be used for categorical data.

An interim summary will be performed when the number of registered cases exceeds 200. The data will be summarized by region and institution. The inclusion criteria for analysis will be reviewed. We will also check for missing values and outliers. Predictors and prediction models will be determined in the final analysis when all cases have been collected.

Multivariate linear and logistic regression models are used to determine the predictors and predictive models for serum 25(OH)D concentration and VDD as outcomes, respectively. The regression coefficients and odds ratios will be calculated, and their 95% confidence intervals and p-values by Wald test will be calculated. Candidate predictors include age, residential area, skin type, smoking status, medication history, habitual drinking, physical activity, the season of blood collection, habitual sun exposure time and frequency, sunscreen use, the experience of suntan within the past 12 months, vitamin D supplement use, the habitual avoidance of sun exposure with parasol use or wearing long sleeve clothes, weekly frequency of vitamin D abundant fish consumption, and cumulative ambient UV-B irradiation.

Two-thirds of the randomly selected data will be used to build the predictive model, and the remaining data will be used to validate the built model. In the test set, variables shown to be significant in the univariate analysis and previously reported predictors are inserted into the multivariate model to construct the predictive model. In the validation set, the predictive performance of the prediction model is checked with the degrees of freedom-adjusted R-squared or AIC for linear regression analysis, and with the c-index for logistic regression analysis. In addition, as model calibration, the predicted and observed values are compared using Cook’s D for linear regression analysis and Hosmer-Lemeshow test for logistic regression analysis. Reporting on the construction of the predictive model will be done following the TRIPOD statement [32].

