## Results and discussion

We plan to register 150 cases each in the summer and winter quarters of 2021–2022. Case registration has been delayed due to the spread of coronaviruses, and 115 cases were collected from 6 institutions by March 2021. We plan to conduct an interim analysis when the number of registered cases reaches 200 or more, and we plan to complete case registration and conduct the final analysis by around September 2022.

The purpose of this study is to determine how serum 25(OH)D concentration in young women is affected by such factors as latitude, season, diet, and lifestyle, and build a prediction model to predict serum 25(OH)D concentrations. The results of this study may provide a scientific basis for the forthcoming Dietary Reference Intakes and other various guidelines. We also plan to develop a tool to screen the risk of VDD and make it available through our website so that individuals can monitor their vitamin D status and easily assess their risk of vitamin D deficiency or insufficiency, which will lead to the prevention of lifestyle-related diseases by improving VDD.

This study is characterized by collecting data on UV-B exposure and lifestyle habits from four different latitudes (seven sites). Although previous reports are available in Japan on the circulating 25(OH)D levels at different latitudes [10,11], they suffer from the narrow range of latitudes [11], and lack of data on UV-B exposure. Another previous study conducted in Hokkaido (43°N) and Kumamoto (33°N) revealed a strong association between latitude and lifestyle [19]. Against this background, we will clarify how latitude and lifestyle affect UV exposure in this study.

There have been some previous papers reporting serum 25(OH)D concentrations in summer and winter, which has yielded conflicting results such as a significant correlation of serum 25(OH)D with UV exposure time and UV energy only in summer [19,20], and significant prediction of 25(OH)D level by UV index but with opposite direction of the association according to the blood collection period [12]. Then, the present study including the determination of serum 25(OH)D concentrations both in summer and winter at different UV irradiance levels together with various demographic variables would be of help clarifying the relationship between ambient UV-B irradiation and serum 25(OH)D levels on a seasonal basis.

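### The 600-woman requirement is not tied to the prediction model it serves, and the stated building rule is likely to give VDD risks that are too extreme, by an amount that depends on coding and predictor strength

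*Protocol article*

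**What the plan says.** Planned size: "The sample size required for this study was calculated to be 600 cases". The inputs given are the prevalence, "assuming that the proportion of VDDs is also 50% in the study population, we expect 300 individuals to have VDDs", and the loss, "we expect 30% of the subjects to drop out of the study due to incomplete data sets and withdrawal of consent". No number of predictors, precision target, events-per-parameter rule or shrinkage target appears.

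Statistical analysis: "Multivariate linear and logistic regression models are used to determine the predictors and predictive models for serum 25(OH)D concentration and VDD as outcomes". The candidate list opens "Candidate predictors include age, residential area, skin type, smoking status, medication history, habitual drinking, physical activity, the season of blood collection" and runs to 15 items, ending with ambient UV-B. On the split, "Two-thirds of the randomly selected data will be used to build the predictive model"; in that part, "variables shown to be significant in the univariate analysis and previously reported predictors are inserted into the multivariate model to construct the predictive model". Odds ratios get Wald intervals and p-values. In the remaining third the logistic model is checked by the c-index and the Hosmer-Lemeshow test. The section does not say what follows if calibration is poor.

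Results and discussion gives the use: "We also plan to develop a tool to screen the risk of VDD and make it available through our website".

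**The concern.** The main product is a risk shown to an individual woman, so the size of the coefficients matters as well as their ranking. When many candidates are screened and fitted by ordinary maximum likelihood on a modest number of events, the fitted log-odds spread too widely in new women: high risks come out too high and low risks too low. The c-index hardly shows this. Screening by univariate significance does not prevent it, because every candidate is tested on the same outcomes that are then used to fit the model.

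A sample size for a prediction model should therefore be tied to the number of candidate parameters. Here 600 is called a calculated requirement without that link, and the building rule contains no correction for overfitting.

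**Working it through.** **The plan's own figure.** 600 × 0.50 = 300 women with VDD. This reproduces, but it follows from 600 and does not derive it. A rule of 10 events per parameter would return 600 only with counts the article never states:
- all 600 used: 300/10 = 30 parameters
- after 30% loss: 600 × 0.70 = 420 women, 210 events, 21 parameters
- after loss and split: 420 × 2/3 = 280 women, 140 events, 14 parameters

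**Building set.** With no loss: 600 × 2/3 = 400 women, 200 events. With the plan's 30% loss: 280 women, 140 events.

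**Candidate parameters.** The article fixes no coding, so the count is a range.
- Low end: 15 counts one term per listed item. About 19 counts separately the items that Table 1 splits (such as weekday and weekend outdoor time), with one linear score each and area as a single term. Keeping area as six categories would add 4 (5 instead of 1).
- High end: every Table 1 category dummy coded. Area 5, skin type 5, drinking 4, outdoor time 4 + 4, sun-exposure frequency 4, sunscreen 4, exercise 3, fish 3, smoking 2, sun avoidance 2, and 1 each for age, season, medication, suntan, supplement and UV-B: total 46.

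**Expected shrinkage.** The standard sizing criterion for a logistic prediction model is n = p / [(S − 1) ln(1 − R²/S)], with p candidate parameters, R² the Cox-Snell R² and S the expected shrinkage factor. It is solved for S. The article gives no R², so 0.15, 0.20 and 0.30 are assumptions. The maximum at 50% prevalence is 0.75, so these are Nagelkerke values of 0.20, 0.27 and 0.40.

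Example: p = 46, n = 400, R² = 0.15. p/n = 0.115; at S = 0.60, (−0.40) × ln(1 − 0.25) = 0.115, so S = 0.60.

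| Building n | p | R² 0.15 | R² 0.20 | R² 0.30 |
|---|---|---|---|---|
| 400 | 15 | 0.82 | 0.86 | 0.91 |
| 400 | 19 | 0.78 | 0.83 | 0.89 |
| 400 | 46 | 0.60 | 0.67 | 0.77 |
| 280 | 15 | 0.76 | 0.81 | 0.87 |
| 280 | 46 | 0.52 | 0.60 | 0.70 |

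Only one cell reaches the usual 0.90.

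**What this means for one woman.** A predicted risk of 80% has log-odds ln 4 = 1.386. With S = 0.82 the corrected log-odds are 1.137, a risk of 76%. With S = 0.60 they are 0.832, a risk of 70%.

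**Parameters supported at S = 0.90.** p = n × (−0.10) × ln(1 − R²/0.90). For R² 0.15/0.20/0.30 this gives about 7/10/16 at n = 400 and 5/7/11 at n = 280.

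**Simulation of univariate screening followed by ordinary logistic regression** (assumed effects, true c-index 0.68 to 0.81). The median calibration slope in new women at n = 400 was 0.72 to 0.84 with 19 linear terms and 0.65 to 0.76 with dummy coding (45 parameters). At n = 280 it was 0.62 to 0.79 and 0.55 to 0.67. A slope of 1 is ideal.

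**The case against.** Three stronger readings are tempting, and the article supports none of them.

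*That the plan lists 46 parameters.* It does not. Its list has 15 items, and the Table 1 column describes how items are tabulated, not how they are modelled. Outdoor time is also recorded in minutes, the text describes four regions where Table 1 has six areas, and some skin types may be nearly empty in this population. So 46 is an upper end, and trend scoring cannot be called a correction of a coding the plan chose.

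*That the model would be overfitted even with all 600 women analysed.* This depends on the count. At n = 600, 15 parameters give 0.87/0.90/0.94, which is at or near the target; 46 give 0.69/0.75/0.83.

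*That the tool would be released with uncorrected coefficients.* The article does not say how the tool's coefficients are finalised. It refers to a separate statistical analysis plan that is not shown and commits to TRIPOD reporting. Shrinkage or recalibration may be specified there.

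It is also fair to say that R² is assumed throughout, and that the article gives neither the number nor the names of the previously reported predictors to be entered.

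What stands: the sizing claim has no stated basis. At the plan's own building sizes, the entry and fitting rule falls short of 0.90 at both ends of the parameter range, except with 15 parameters, 400 women and the strongest assumed R². The validation third (200 women, or 140 after loss) may reveal miscalibration, but no response to it is stated.

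**Conclusion.** The point holds in this limited form. The requirement of 600 is not derived from anything the article gives and is not linked to the models. Followed as written, the building rule is likely to yield individual VDD risks that are too extreme. The direction is fairly firm; the size is not. Expected shrinkage ranges from 0.91 at best (15 parameters, 400 women, R² 0.30) to 0.52 at worst (46 parameters, 280 women, R² 0.15). It rests on assumed R² values, on an unstated coding, and on reading the stated regression with Wald inference as an ordinary fit. The calculation covers the VDD logistic model only; the linear model for 25(OH)D concentration is not quantified here.

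**What to change.** In Statistical analysis, add that the tool's VDD coefficients are corrected for overfitting before release, by one of two routes:
- a bootstrap shrinkage factor, with the univariate selection step repeated in every bootstrap sample; or
- penalised logistic regression, with the penalty chosen by cross-validation within the building data.

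Keep ordinary regression with Wald intervals for the association tables. If the separate analysis plan already does this, a sentence in the protocol saying so is enough.

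In Planned size, replace the claim that 600 was calculated as required with a statement of how many candidate parameters the building set supports under stated R² assumptions, for example the 7/10/16 (400 women) and 5/7/11 (280 women) shown above.

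As an indication only, a simple fixed ridge penalty in a separate simulation of the univariate screen at n = 400 (true c-index 0.70 to 0.78) raised the median slope from 0.69–0.78 to 0.89–1.02, with the c-index essentially unchanged. The two routes proposed here were not themselves simulated.

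Cost: plan wording and a little more analysis, with no extra participants or data. The shrunken tool coefficients carry no Wald intervals.

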Statistical significance will be set at a two-tailed p-value < 0.05 for all analyses. All statistical analyses will be performed according to the statistical analysis plan decided before the analysis.

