A previous study has reported that the use of sunscreens and sun protection tools did not affect serum 25(OH)D concentrations in multivariate regression models [19]. This paper, however, included both sexes, which can be a confounding variable, and reports on the effect of the use of sunscreens and sun protection tools on serum 25(OH)D concentrations are quite limited in young women except in pregnant women [11]. Then, the study design of the present study including only women can rather be a strength, and suited for clarifying the effect of use of sunscreen and sun protection tools reduce serum 25(OH)D concentrations.

Individual UV irradiation dose can be evaluated either by direct measurement or estimation. As the former, the use of wearable devices is useful enabling a more accurate assessment of individual UV doses, which, however, is a burden to the participants. Then, we have not adopted such devices, and estimate the UV exposure for each region. The association of estimated UV irradiation dose and serum 25(OH)D levels has previously been reported [12,13]. For example, Cardoso et al [12] used the UV index obtained from the Portuguese Institute of Oceanography and Atmospheric Research. O’Sullivan et al. estimated the cumulative and weighted daily ambient dose of UV-B at wavelengths where vitamin D synthesis is possible [13].

Much more strong association between the dietary vitamin D intake and serum 25(OH)D levels could be expected than that in European and American studies, with the possible bases described below. Previous European reports on the ultraviolet effects on vitamin D status had a methodological flaw; no data on dietary vitamin D intake [12,13]. Another important issue to be considered is the markedly different prevalence of subjects under vitamin D supplementation between Europe and Japan. It was as high as 49.9% in the European study [13], whereas it was only 5.1% in a Japanese study for pregnant women with an age distribution similar to that in our study [11]. In the above-mentioned European studies, it is quite likely that the overwhelming effects of supplementation have obscured the contribution of dietary vitamin D. In Japan with a much lower percentage of vitamin D supplementation, a strong association between dietary vitamin D intake and serum vitamin D concentration could be expected, unlike the results from European and American studies.

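### The univariate p<0.05 screen may drop a masked predictor such as sunscreen use, and leaves the Wald intervals of the predictors it admits unreliable

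*Protocol article*

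**What the plan says.** The Statistical analysis section of the protocol article gives the entry rule for both the linear and the logistic model: "variables shown to be significant in the univariate analysis and previously reported predictors are inserted into the multivariate model". There are two routes in, univariate significance or an earlier report. The threshold for the first comes from the end of the same section: "Statistical significance will be set at a two-tailed p-value < 0.05 for all analyses". The article does not name the variables that enter by the second route.

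For the regression coefficients and odds ratios, "their 95% confidence intervals and p-values by Wald test will be calculated". No correction for selection is described. On the data used, "Two-thirds of the randomly selected data will be used to build the predictive model", and the remaining third is for validation.

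Sunscreen use and avoidance of sun by parasol or clothing are listed candidates. In Results and discussion the article reports an earlier study in which "the use of sunscreens and sun protection tools did not affect serum 25(OH)D concentrations in multivariate regression models", and describes its own women-only design as "suited for clarifying the effect of use of sunscreen and sun protection tools".

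**The concern.** A univariate screen decides on the crude association, before any adjustment. The questions in Results and discussion (how latitude, season, diet, lifestyle and sun protection affect 25(OH)D) concern adjusted effects. The two can differ sharply here. The article says that summer and winter correspond to the highest and lowest 25(OH)D. If women use more sunscreen in summer, or when they spend longer outdoors, a lowering effect of sunscreen is offset in the crude comparison and may not reach p<0.05. By the same mechanism, a variable with no effect of its own may pass because it tracks season.

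The second route does not clearly protect sunscreen, because the one earlier result that the article describes for it is null.

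The other consequence concerns inference. When a predictor is in the model because it was significant in the same data, its Wald interval and p-value no longer have their nominal meaning. At stake are the answer to a question the authors single out and the reliability of the reported coefficients.

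**Working it through.** **Sample available.** The Planned size section states "The sample size required for this study was calculated to be 600 cases" and "assuming that the proportion of VDDs is also 50% in the study population, we expect 300 individuals to have VDDs". This reproduces: 600 × 0.50 = 300, before losses. If the expected 30% loss applies to the 600, then 600 × 0.70 = 420 remain, and two-thirds of 420 is 280. Without loss, the build set is 400.

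**Check 1: masking by outdoor time.** Assumed, since the documents give no effect sizes or correlations: all variables standardised, outdoor time +0.25, sunscreen -0.15, correlation r between them, n = 280.

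- Crude sunscreen effect: m = -0.15 + 0.25r. Screening z = |m| × √(n/(1 - m²)).
- Adjusted test: residual SD s = √(1 - 0.085 + 0.075r), where 0.085 = 0.25² + 0.15² and 0.075 = 2 × 0.25 × 0.15. Then z = 0.15 × √(n(1 - r²))/s.
- Each probability is that of exceeding 1.96 in absolute value, by the normal approximation.

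| r | crude m | screening z | passes screen | adjusted z | significant when adjusted |
|---|---|---|---|---|---|
| 0.5 | -0.025 | 0.42 | 7% | 2.23 | 60% |
| 0.25 | -0.0875 | 1.47 | 31% | 2.51 | 71% |
| 0.1 | -0.125 | 2.11 | 56% | 2.60 | 74% |
| 0 | -0.15 | 2.54 | 72% | 2.62 | 75% |
| -0.25 | -0.2125 | 3.64 | 95% | 2.57 | 73% |

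At r = 0.5, s = √0.9525 = 0.976 and the adjusted z is 0.15 × √(280 × 0.75)/0.976 = 2.23. With all 420 women, adjusted power is 78%.

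**Check 2: masking by season, by simulation.** Assumed: residual SD 6 ng/mL, summer 6 ng/mL above winter, sunscreen effect 0 to -3 ng/mL, sunscreen use in summer/winter of 50/50%, 70/40% or 75/35%; 4,000 runs per scenario. Sunscreen was screened alone at p<0.05 and then fitted with season.

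Take a true effect of -2 and 70/40% use, with equal numbers in each season. The summer share is 0.35/0.55 = 0.636 among users and 0.15/0.45 = 0.333 among non-users. The crude effect is then -2 + 6 × 0.303 = -0.18, almost nothing.

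| true effect | use by season | passes screen, n=280 | n=400 |
|---|---|---|---|
| -2 | unrelated | 71% | 84% |
| -2 | 70/40 or 75/35 | 5–9% | 6–10% |
| -3 | unrelated | 96% | 99% |
| -3 | 70/40 or 75/35 | 11–32% | 14–44% |
| 0 | 70/40 or 75/35 | 62–86% | 77–95% |

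For -2 with 70/40% use, the season-adjusted test was significant in 74% of runs at n = 280 and 88% at n = 400, while the screen admitted sunscreen in 5% and 6%. The last row shows the opposite error: a variable with no effect is usually admitted.

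**Check 3: intervals after screening.** Coverage of the nominal 95% interval from the season-adjusted model, counting only runs in which the screen admitted sunscreen:

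- null effect, not confounded: 42–46%
- -1, not confounded: 90–91%; -1, confounded: 84–96%
- -2, confounded: 53–70%
- -3, confounded: 80–94%
- -2 or -3 not confounded, and null confounded by season: 96–97%

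With no screen, coverage was 94–96% in every scenario.

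**The case against.** The strongest objection is the second route. A previously reported predictor enters whatever its univariate p-value, and sunscreen may count as one. The article mentions a report in pregnant women whose direction it does not state, and its sun-exposure items come from a published, validated questionnaire. The analysis plan it refers to is not shown and may list the forced-in variables. This stands. A reader might infer that the plan removes sunscreen; the documents do not support that, only that its entry is not assured.

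Second, the masking depends on an assumed positive correlation. If women who avoid the sun are also those who use sunscreen, the correlation is negative and the crude effect is strengthened: 95% pass at r = -0.25. This also stands, so the 7% is one end of a range.

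Third, a reader might infer that all the reported intervals are invalid, always too narrow and with p-values too small. That goes too far. Predictors entered by prior report are not chosen by the screen, and for screened-in predictors coverage ranged from about 42% to nominal. The article also does not say outright that the intervals come only from the build set, although this is the natural reading.

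Fourth, the held-out third checks predictive performance on data not used for selection. True, but it does not repair the intervals or return a dropped predictor.

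Finally, forcing every candidate into one model would cause its own trouble. The section on cumulative ambient UV-B computes it by recruitment site and date under a cloudless sky, so it is largely determined by area and season. The fix has to allow for that.

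**Conclusion.** The concern holds in a limited form. The univariate screen is a method that the article states, not a detail left to an analysis plan. It may drop a predictor masked by season or outdoor time and may admit one that merely reflects them. Sunscreen and sun protection are the clearest case, because the study claims to be suited to clarifying their effect and the only earlier result described is null.

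The size depends on inputs that the documents do not give. Under the assumed standardised effects at n = 280, the chance of passing the screen runs from 7% to 72% as the correlation with outdoor time falls from 0.5 to 0, while adjusted power stays between 60% and 75%. The loss is large with strong positive correlation, small with none, and absent when the correlation is negative. Nominal Wald intervals and p-values for screened-in predictors cannot be relied on, to a degree that varies with the true effect and the confounding.

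**What to change.** Drop the univariate p-value screen and fix the predictor list before analysis, from the candidates already named in the Statistical analysis section. Always include sunscreen and sun protection, outdoor time, season and diet.

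Keep the two purposes apart:

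- For the prediction models, use shrinkage such as ridge on the prespecified list.
- For the stated questions on sun protection, season, latitude, diet and lifestyle, take confidence intervals from a prespecified adjusted model with no data-driven selection.

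Because UV-B is computed by site and date, state in advance how UV-B, area and season are represented, for example in separate models, instead of forcing all three into one.

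The cost is analysis wording and standard software, with no new data. The models carry a few more terms, and some intervals will be somewhat wider.

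### For the linear 25(OH)D model, Cook's D cannot show calibration, and adjusted R-squared or AIC do not properly measure held-out accuracy

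*Protocol article*

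**What the plan says.** The protocol article, under Statistical analysis, assigns a random two thirds of the data to model building. Of the other third it says that "the remaining data will be used to validate the built model". For the linear model in this validation part, "the predictive performance of the prediction model is checked with the degrees of freedom-adjusted R-squared or AIC for linear regression analysis"; the logistic model for vitamin D deficiency (VDD) is scored there with the c-index. As the calibration step for the two models, "predicted and observed values are compared using Cook’s D for linear regression analysis and Hosmer-Lemeshow test for logistic regression analysis". The section commits to TRIPOD reporting and refers to a separate statistical analysis plan, which is not available here.

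Under Planned size: "The sample size required for this study was calculated to be 600 cases". The reasoning given is "assuming that the proportion of VDDs is also 50% in the study population, we expect 300 individuals to have VDDs", followed by "we expect 30% of the subjects to drop out of the study due to incomplete data sets and withdrawal of consent".

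Under Results and discussion, the sponsor intends a website tool with which individuals can assess their own VDD risk, and expects the results to inform dietary reference intakes.

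**The concern.** A prediction model is validated by fixing its equation, applying it to data that played no part in fitting, and measuring how close the predictions come (accuracy) and whether they are systematically too high, too low or too extreme (calibration). For the linear model, the statistics named do neither job properly. Cook's D is an influence diagnostic. Adjusted R-squared and AIC are built for the sample in which the coefficients were estimated. The text also leaves open which of the two will be used.

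At stake is the study's main product. If the text is followed literally, the 25(OH)D equation has no valid calibration figure, and its accuracy figure is either distorted or belongs to another model. For the logistic model the question is narrower: whether a Hosmer-Lemeshow test alone says enough about calibration in a validation set of this size.

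**Working it through.** **1. Size of the validation set.** Inputs from Planned size and Statistical analysis: 600 participants, 50% VDD, 30% loss, one third held out.
- The plan's own figure: 600 × 0.50 = 300 with VDD. It reproduces.
- Analysable after loss: 600 × 0.70 = 420. Development: 420 × 2/3 = 280. Validation: 420 / 3 = 140, about 70 with VDD.
- Upper bound with no loss: 600 / 3 = 200, about 100 with VDD.

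**2. Cook's D.** For observation i, D = [e² / (p s²)] × [h / (1 − h)²], where e is the residual, h the leverage, p the number of coefficients and s² the residual variance of the fit. It measures how far the fitted values move when that observation is deleted. Leverage and residual variance belong to a fit, so computing it in validation data means refitting there. After a refit, a constant error in the original predictions is absorbed by the new intercept and leaves every D unchanged. This part needs no numerical assumption.

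**3. Adjusted R-squared with a frozen model.** Formula: 1 − (1 − R²)(n − 1)/(n − p − 1). Take a held-out R² of 0.30 (assumed) and n = 140:
- p = 10: 1 − 0.70 × 139/129 = 0.25
- p = 20: 1 − 0.70 × 139/119 = 0.18

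At n = 200:
- p = 10: 1 − 0.70 × 199/189 = 0.26
- p = 20: 1 − 0.70 × 199/179 = 0.22

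The term counts are assumptions; the protocol lists candidates but fixes no final number. No coefficient is estimated in the validation data, so there is nothing to penalise, and the unadjusted 0.30 is the right figure.

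**4. Refitting in the validation third.** Simulation with 500 replicates, 280 development and 140 validation subjects. Assumptions: 25 terms fitted, 5 of them real with coefficient 1.5 per SD, residual SD 6 ng/mL, both parts from the same population. Averages:

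| Statistic | Value |
|---|---|
| Adjusted R², development fit | 0.24 |
| Adjusted R², refitted in validation data | 0.24 |
| R² of the frozen equation in validation data | 0.16 |
| Calibration slope of the frozen equation | 0.78 |

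The refit returns the development figure and hides the overfitting that the frozen R² and the slope reveal. Penalising the frozen value instead gives 1 − 0.844 × 139/114 = −0.03. So a model whose held-out R² is 0.16 would be reported as 0.24 or −0.03, depending on how the same sentence is read. AIC is meaningful only relative to another model on the same data, so it gives no absolute accuracy on either reading.

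**5. Hosmer-Lemeshow for the logistic model.** Simulation with 10 groups by predicted risk, frozen predictions, chi-square on 10 df, alpha 0.05 and a normal linear predictor whose SD is assumed. Power for a calibration slope of 0.7 (8,000 runs per cell):

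| n | SD 0.8 | SD 1.0 | SD 1.2 | SD 1.5 |
|---|---|---|---|---|
| 140 | 14% | 18% | 25% | 34% |

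At n = 200 the range over the same SDs is 17-40%. A separate set of 3,000 runs agrees: 14% and 24% at n = 140 for SD 0.8 and 1.2. For a slope of 0.5 at n = 140, power is about 30-33% at SD 0.8, 61-62% at SD 1.2 and 78% at SD 1.5.

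**The case against.** The strongest defence has five parts.

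- **The c-index.** A reader might infer that none of the listed statistics validates anything. That is not so: the c-index in held-out data is a proper measure of discrimination, and the logistic model is the one closest to the screening tool. This stands in full.
- **Hosmer-Lemeshow.** It does compare observed with predicted events. A reader might infer that the sponsor will treat a non-significant result as proof of calibration, or will use 8 df and so inflate false positives. The protocol says neither. Nor can it be said that a badly overfitted model would pass: step 5 shows a slope of 0.5 is often detected if predicted risks are widely spread. The test is therefore weak for moderate miscalibration, not wrong.
- **Size of the adjusted R-squared effect.** The protocol fixes no term count. With 8 terms the 0.30 becomes 1 − 0.70 × 139/131 = 0.26, a small change. With a frozen model the penalty understates performance, and the unadjusted value can be recovered from n and p. This limits the harm on that reading but does not make the statistic right. The refit reading errs in the flattering direction.
- **Large systematic errors.** One might infer that errors of several ng/mL could go unseen. Refitted statistics are blind to them, but the split is random within one sample. Under the assumptions of step 4, the mean held-out error would vary with an SD of only about 0.65 ng/mL, so an error of 3-8 ng/mL is not to be expected.
- **The separate analysis plan.** It may contain further measures, so it cannot be said that the model will be published without a valid figure. But the protocol article does not leave this matter open. It names the measures and names them wrongly, so the point is not an omission.

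**Conclusion.** The point holds for the linear 25(OH)D model and is wrong as written. Describing Cook's D as a comparison of predicted with observed values is an error on any assumption. Adjusted R-squared and AIC are unsuitable in held-out data on either reading: the penalty is misplaced if the equation is frozen, and a different model is assessed if it is refitted. How far the reported figure is off depends on the number of terms and the true R-squared, neither of which the documents give.

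For the logistic model there is no error to correct. The c-index is sound. Hosmer-Lemeshow is a legitimate but low-powered check with 140, or at most 200, validation subjects, and it gives neither the size nor the direction of miscalibration. The power figures rest on an assumed linear-predictor SD of 0.8-1.5. The additions for this model are an inexpensive improvement.

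**What to change.** Rewrite the validation sentences under Statistical analysis, and bring the analysis plan into line before the final analysis.

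- **Linear model:** apply the development equation, with coefficients frozen, to the validation third. Report out-of-sample R-squared (1 − SSE/SST), RMSE or MAE in ng/mL, calibration intercept and slope with 95% CI, and a predicted-versus-observed plot. Do not refit or use AIC in the validation data. Keep Cook's D as an influence diagnostic during model building only.
- **Logistic model:** keep the c-index. Add the calibration intercept and slope with 95% CI and a calibration curve. If Hosmer-Lemeshow is retained, state that a non-significant result is not evidence of good calibration.

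The cost is one reworded paragraph and a few lines of code. Recruitment, sample size and data collection are unchanged.
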